## Abstract

**Background:**

Premature Ventricular Complexes (PVCs) are very common in clinical practice, with frequent PVCs (more than 30 beats per hour) or polymorphic PVCs significantly increasing the risk of mortality. Previous studies have shown that vagus nerve stimulation improves ventricular arrhythmias. Stimulation of the auricular distribution of the vagus nerve has proven to be a simple, safe, and effective method to activate the vagus nerve. Transcutaneous au ricular vagus nerve stimulation (taVNS) has shown promise in both clinical and experimental setting for PVCs; however, high-quality clinical studies are lacking, resulting in insufficient evidence of efficacy.

**Methods:**

The study is a prospective, randomized, parallel-controlled trial with a 1:1 ratio between the two groups. Patients will be randomized to either the treatment group (taVNS) or the control group (Sham-taVNS) with a 6-week treatment and a subsequent 12-week follow-up period. The primary outcome is the proportion of patients with a ≥ 50% reduction in the number of PVCs monitored by 24-hour Holter. Secondary outcomes include the proportion of patients with a ≥ 75% reduction in PVCs, as well as the changes in premature ventricular beats, total heartbeats, and supraventricular premature beats recorded by 24-hour Holter. Additional assessments compared score changes in PVCs-related symptoms, as well as the score change of self-rating anxiety scale (SAS), self-rating depression scale (SDS), and 36-item short form health survey (SF-36).

**Discussion:**

The TASC-V trial will help to reveal the efficacy and safety of taVNS for frequent PVCs, offering new clinical evidence for the clinical practice.

**Trial registration:**

Clinicaltrials.gov: NCT04415203 (Registration Date: May 30, 2020).

**Supplementary Information:**

The online version contains supplementary material available at 10.1186/s12906-024-04568-1.

## Background

Premature ventricular complexes (PVCs) are the ectopic beats of the ventricular muscle, which are very common even in population without any abnormal structure of the heart. The detection of PVCs is 40–75% through the 24-hour or 48-hour Holter [1, 2], and that figure for frequent PVCs is around 7.7% through 24-hour Holter [2]. Predictor studies have shown that low education status, smoking, large waist-to-hip ratio, less exercise, taller height, older age, etc. were associated with an increased risk for [3, 4]. Frequent PVCs are stated as no less than 1 PVCs detected by a 12-lead Electrocardiograph, or more than 30 PVCs per hour [5]. More and more studies have revealed that in population with no abnormalities in cardiac structure, frequent PVCs affected the function and structure of left atrial and left ventricular disadvantagely [6], and were associated with the increased risk of cardiovascular risk or death [4, 5, 7]. Patients with frequent PVCs are usually with no symptoms. However, some of them could have desultory fatigue, dizziness, labored breathing and palpitations [8]. More serious, continuously developed PVCs can lead to ischemic cardiomyopathy, non-persistent or persistent ventricular tachycardia, and even heart failure [9]. β-blockers and non-dihydropyridine calcium channel blockers are still the first-line medicines for PVCs [10]. Moreover, the applicable population and side-effects should be noticed. Catheter ablation would be suggested if medication failed. Nonetheless, the application is limited due to its strict indications and high price. Therefore, it is worthwhile to seek a therapy that is effective, well-tolerant, and with few side effects in addition to agents.

Increasing research indicated that there was rich vagal innervation in the ventricle [11], especially in the ventricular myocardium and the ventricular conduction system [12]. It has been shown that vagus nerve stimulation can improve ventricular rhythm [13]. The auricular branch is the only cutaneous mucocutaneous branch of the vagus nerve, and the stimulation in the ear’s distribution area could effectively activate the vagus nerve [14].

Transcutaneous auricular vagus nerve stimulation (taVNS) is a non-invasive and safe physical therapy, which could stabilize the heart rhythm by stimulating the vagus nerve [15]. The vagus nervous system belongs to the autonomic nervous system, and the heart is regulated by the autonomic nervous system. Dysregulation of the autonomic nervous system, such as decreased vagal activity and increased sympathetic activity, can lead to arrhythmias and more serious cardiovascular diseases [16]. The autonomic nervous system can be regulated by taVNS, which could further enhance the excitability of the vagus nerve, inhibit the activity of the sympathetic nerve, and bring the autonomic nervous system to a balanced state [16]. In addition, taVNS has been shown to reduce ventricular interstitial fibrosis, reduce the possibility of ventricular arrhythmias, and stabilize the electrophysiological conduction of cardiomyocytes in models of heart diseases such as myocardial infarction and heart failure [17]. The auricular point CO15 (Xin) is in the concha cavity, and HX1 (Erzhong) is in the middle point of the helix, both are in the area of auricular vagus nerve distribution [18]. Stimulating on these two points can modulates the excitability of the vagus nerve [19]. Besides, laboratory studies have shown that needling in PC6 (Neiguan) and HT7 (Shenmen) stabilizes heart rate by blocking ion channels in tachyarrhythmia cardiomyocytes and stimulating parasympathetic nerves [20–22].

Although there was clinical and experimental basis of taVNS for PVCs, but the high-quality clinical studies are limited with insufficient evidence of efficacy. This study preliminarily evaluated the efficacy of taVNS in reducing the number of PVCs in patients with frequent PVCs, and evaluated the acceptability and safety of patients, laying a foundation for further clinical research.

## Methods

### Study design

This is a randomized controlled trial, which is carrying out at three centers in China: Guang’anmen Hospital, China Academy of Chinese Medical Sciences, Peking University Third Hospital Yanqing Hospital and Beijing Longfu Hospital. This trial was started on June 4th, 2020, and will be completed in June 2024 anticipatedly. The flow chart and flow sheet are showed in Fig. 1; Table 1.

**Fig. 1 Fig1:**
[figure not shown]
Flowchart of Study PVCs: premature ventricular complexes; taVNS: Transcutaneous auricular vagus nerve stimulation

**Table 1 Tab1:** Study schedule by time

Period	Baseline	Treatment						Follow-up		
**Week**	**-1**	**1**	**2**	**3**	**4**	**5**	**6**	**10**	**14**	**18**
Screening	**×**									
Informed consent	**×**									
Demographic data	**×**									
Eligibility	**×**									
Factors that affect heart rate	**×**	**×**	**×**	**×**	**×**	**×**	**×**	**×**	**×**	**×**
History of present illness	**×**									
Previous treatment history	**×**									
Vital signs	**×**	**×**	**×**	**×**	**×**	**×**	**×**	**×**	**×**	**×**
Complete blood analysis	**×**									
Cardiac B ultrasound	**×**									
24-hour Holter	**×**						**×**			**×**
Total cardiac impulse by 24-h Holter	**×**						**×**			**×**
Premature ventricular contractions by 24-h Holter	**×**						**×**			**×**
Supraventricular premature contractions by 24-h Holter	**×**						**×**			**×**
Combined treatment/medication	**×**	**×**	**×**	**×**	**×**	**×**	**×**	**×**	**×**	**×**
VAS for PVC-related symptoms	**×**	**×**	**×**	**×**	**×**	**×**	**×**	**×**	**×**	**×**
Self-rating anxiety scale (SAS)	**×**						**×**			**×**
Self-rating depression scale (SDS)	**×**						**×**			**×**
The short form health survey (SF-36)	**×**						**×**			**×**
Evaluation of treatment associated adverse events		**×**	**×**	**×**	**×**	**×**	**×**			
Evaluation of adherence							**×**			
Evaluation of acceptability							**×**			

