### Blinding

Acupuncturists could not be blinded for that the taVNS is a manipulating intervention. The participants, outcome evaluator and statistician are blinded. Patients will accept taVNS in the treatment group, and sham-taVNS without any current output in the controlled group. For the blinding, patients in both groups were told that the feelings of stimulation they would receive might vary individually, with some could feel it and others could not feel it at all. During the treatment, the sound of adjusting the current was the same in both groups.

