Secondary outcomes include: (1) the proportion of participants with a ≥ 50% decrease of PVCs from baseline at the end of week 18 and the proportion of participants with a ≥ 75% decrease of PVCs from baseline at the end of week 6 and 18 which will be assessed the same way as the primary outcome; (2) the change from baseline in PVCs, total cardiac impulse and supraventricular premature contractions at the end of week 6 and 18 which will also be assessed through a 24-h Holter; (3) the score change from baseline in the symptom of palpitation, chest tightness, dizziness or insomnia at the end of week 6 and 18; the change of the proportion of participants with moderate/severe symptoms of palpitation, chest tightness, dizziness or insomnia from baseline at the end of week 6 and 18; The symptom of palpitation will be assessed by a 10-scale VAS from 0 to 10, a higher score indicates a more severe symptom; Score 4–6 are defined as the moderate level, Score 7–10 are defined as the severe level; (4) the score change from baseline in the Self Anxiety Scale (SAS) at the end of week 6 and 18. SAS contains 20 items scoring from 25 to 100. The higher the score significates the greater anxiety. (5) the score changes from baseline in the Self Depression Scale (SDS) at the end of week 6 and 18. SDS contains 20 items scoring from 25 to 100. The higher the score significates the greater depression. (6) the score changes from baseline in 36-Item Short Form Health Survey (SF-36) at the end of week 6 and 18. The SF-36 questionnaire contains eight scales with two measures: physical and mental health. The physical health includes four scales of physical functioning, role-physical, bodily pain, and general health. The mental health is composed of vitality, social functioning, role emotional, and mental health. SF-36 scores from 0 to 100, higher scores indicate better health status.7) subgroup analysis of ages (classified as ≤ 40 years and > 40 years), sex and the severity of PVCs (classified as Grade 2, 3, and 4 A according to Lown grading system) on the primary outcome. 8) the proportion of participants with treatment-related adverse events between two groups.

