## Conclusion

The TASC-V trial will reveal the efficacy and safety of taVNS for frequent PVCs, and provide new clinical evidence for the clinical practice.

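### Adverse events are scheduled for evaluation only in weeks 1–6 and compared only if treatment-related, while efficacy runs to week 18 and the conclusion claims safety without that limit

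*Protocol article*

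**What the plan says.** The Abstract describes a trial "with a 6-week treatment and a subsequent 12-week follow-up period", and the last column of Table 1 is week 18.

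Table 1 has one adverse-event row, "Evaluation of treatment associated adverse events". It is marked at each of weeks 1 to 6 and is empty at weeks 10, 14 and 18. Vital signs, factors affecting heart rate, "Combined treatment/medication" and "VAS for PVC-related symptoms" are marked at all three of those visits. The "24-hour Holter" row is marked at baseline, week 6 and week 18.

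The Outcome section lists one safety outcome, its item 8: "the proportion of participants with treatment-related adverse events between two groups". No time point is attached, although the Holter, symptom and questionnaire outcomes in the same list carry weeks 6 and 18 or a stated week.

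The last paragraph of the Background names safety as an aim. The Discussion says the trial assesses both short-term and long-term effects. The Conclusion states: "The TASC-V trial will reveal the efficacy and safety of taVNS for frequent PVCs".

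**The concern.** The plan follows benefit for three times as long as harm. Efficacy can be reported at week 18, but the adverse-event comparison ends with the last treatment week, and nothing in the aim or the Conclusion tells the reader so.

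Two limits apply together. The first is the window: an event first occurring between weeks 7 and 18 has no scheduled adverse-event evaluation, whatever its cause. The second is attribution: an event in weeks 1 to 6 that is judged unrelated falls outside the stated outcome. In a randomised sham-controlled trial the all-event comparison by arm is the one that needs no causality judgement, and it is not among the listed outcomes.

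The Background itself says that frequent PVCs can progress to ventricular tachycardia and heart failure. If such an event occurred during follow-up, the stated comparison would not count it. A favourable safety statement at week 18 would then rest on data from weeks 1 to 6.

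**Working it through.** **Inputs.** Treatment 6 weeks and follow-up 12 weeks (Abstract, Methods); visit marks (Table 1); safety outcome (Outcome, item 8); recording of withdrawal reasons (Quality control).

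**Step 1: length of observation.** 6 + 12 = 18 weeks, which agrees with the last column of Table 1.

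**Step 2: share of time without scheduled adverse-event evaluation.** 12 / 18 = 0.667, or 67%.

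**Step 3: share of visits.** The post-baseline columns are weeks 1, 2, 3, 4, 5, 6, 10, 14 and 18, which makes 9. The adverse-event row is blank in 3 of them: 3 / 9 = 0.333, or 33%.

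**Step 4: what else follow-up collects.**

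| Table 1 row | Weeks 1–6 | Week 10 | Week 14 | Week 18 |
|---|---|---|---|---|
| Adverse events | all six | – | – | – |
| Vital signs | all six | yes | yes | yes |
| Factors affecting heart rate | all six | yes | yes | yes |
| Concomitant treatment | all six | yes | yes | yes |
| Symptom VAS | all six | yes | yes | yes |
| Holter | week 6 only | – | – | yes |

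Four safety-relevant rows are filled at 3 of 3 follow-up visits, and the Holter at 1 of 3. Under Quality control, dropouts and withdrawals are documented with reasons for the whole trial.

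**Step 5: set schedule, outcome and claim side by side.** Item 8 gives no time point, so its window comes from Table 1 alone: six weeks. The follow-up rows in Step 4 feed efficacy outcomes (Holter counts and symptom scores at week 18) or serve as background records. No stated safety outcome uses them. The Conclusion mentions neither the six-week window nor the restriction to related events.

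**The case against.** **Follow-up is not empty of safety information.** A reader might infer from the blank row that two thirds of the trial yields no safety data. The document does not support that. Step 4 shows vital signs, symptoms and treatment recorded at every follow-up visit and a Holter at week 18. A procedure during follow-up could appear under concomitant treatment, and an event that led to withdrawal should appear with its reason. This part of the objection stands in full. What remains is that these data are not part of the safety comparison.

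**Bias by unblinded operators is not shown.** The Blinding section says "Acupuncturists could not be blinded for that the taVNS is a manipulating intervention", and a reader might infer that relatedness is judged by someone who knows the arm. The next sentence says that participants, outcome evaluator and statistician are blinded, and nothing assigns the causality judgement to the acupuncturist. If the evaluator makes it, that route to bias largely closes. The restriction to related events still stands.

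**A journal article condenses.** Definitions, causality procedure and serious-event reporting may be in the full protocol, and their absence here is no fault. Nor does naming related events as the outcome show that other events go unrecorded. The point, however, rests on a schedule and an outcome that the article does state. Serious-event reporting elsewhere would not by itself change either.

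**It is a recognisable choice, and the claim is modest.** Tying adverse-event evaluation to the period of device use is defensible. The Conclusion is prospective, the study is called preliminary, and the Discussion concedes a small sample and short follow-up. All this lowers the severity. It does not supply the missing limit, because the safety aim and the Conclusion are not confined to the treatment period.

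**It may be late.** Completion was expected in June 2024, so adding a visit question may help few participants. The analysis and wording changes do not depend on that.

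**Conclusion.** The point holds as a gap in coverage. Adverse-event evaluation is scheduled for 6 of 18 weeks and 6 of 9 post-baseline visits, and the only safety outcome counts treatment-related events. Efficacy is followed to week 18, and the Conclusion speaks of safety without either limit.

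The size is 67% of the time, or 33% of the visits. Both figures should be given, because the first alone makes the gap look larger than the visit schedule does. Neither says how many events would be missed, and the document gives no event rates from which to estimate that.

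This assumes that Table 1 is the operative schedule and that no fuller document extends adverse-event evaluation into follow-up or adds an all-event comparison. It does not assume that follow-up lacks safety data or that relatedness is judged unblinded, since the article supports neither. It is an inexpensive improvement worth making, and it does not threaten the primary analysis.

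**What to change.** 1. For participants still in follow-up, mark the adverse-event row of Table 1 at weeks 10, 14 and 18.
2. State the safety outcome as all recorded adverse events compared by arm, regardless of judged relation, and give it a time window. Keep treatment-related events as a subset, with relatedness judged by the already blinded outcome evaluator.
3. For participants who have finished, search the existing follow-up visit, medication and withdrawal records for events. Report what was recovered in this way separately from what was asked prospectively.
4. Where follow-up events cannot be recovered, limit the safety statement to the six-week treatment period, in the Conclusion and in the results paper.

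The cost is one case-report-form line at visits that already take place, plus a review of existing records. The main drawback is that data after week 6 will be incomplete for participants who have already finished. Item 4 costs only a change of wording and is possible at any stage before publication.

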### Randomization

The random number was generated by a statistician from Clinical Pharmacological Assessment Center of Guang’anmen Hospital by using SAS software through PROC PLAN statement. The random codes were sealed in opaque envelopes and be placed in order according to the serial numbers outside. A staff who was not involved in the treatment and evaluation of this trial keeps these envelopes and is responsible for the assignment.

### Blinding

Acupuncturists could not be blinded for that the taVNS is a manipulating intervention. The participants, outcome evaluator and statistician are blinded. Patients will accept taVNS in the treatment group, and sham-taVNS without any current output in the controlled group. For the blinding, patients in both groups were told that the feelings of stimulation they would receive might vary individually, with some could feel it and others could not feel it at all. During the treatment, the sound of adjusting the current was the same in both groups.

### Participants

Patients with PVCs will be evaluated for the enrollment. The inclusion criteria contain: (1) diagnosed as the frequent premature ventricular contraction (>720 PVCs through 24 h-Holter) [5] with the Lown grading system of 2, 3 and 4 A [23]; (2) 18 years ≤ age ≤ 75 years; (3) volunteered to participant. Patients will be excluded if they (1) have severe valvular heart disease, congenital heart disease, pericardial disease, hypertrophic cardiomyopathy, unstable angina, acute myocardial infarction, myocarditis, aneurysm, congestive heart failure decompensation period (New York Heart Association classification of III or VI), cardiogenic shock, cerebrovascular disease, hematopoietic system disease, severe mental disease; (2) have bradycardia, including pathologic sinus node syndrome, atrioventricular block no less than the second degree; (3) have already had pacemaker or percutaneous coronary intervention, or who plan to have pacemaker or percutaneous coronary intervention; (4) are female during pregnancy or lactation; (5) have sensory loss; (6) are allergic to electric current or transcutaneous patches; (7) blood pressure ≤ 90/60 mmHg; (8) participate in other clinical trials within 3 months before the screening.

### Intervention

Two to three acupuncturists from each site with no less than 2 years of acupuncture experience manipulate the taVNS or sham-taVNS. All acupuncturists are the registered practitioners of traditional Chinese medicine. The acupuncturists and outcome evaluators received a systemic training before the recruitment. Both treatments are constitutive of 30 sessions over 6 weeks with 30 min for each session, 5 sessions per week. Huato disposable ear clip electrodes, skin electrodes and Huato SDZ-IIB stimulator will be used (Suzhou Medical Appliance, Suzhou, China). Intervention procedures of the taVNS and sham-taVNS are showed in Figs. 2 and 3.

#### taVNS group

Participants in taVNS group will receive taVNS and usual care. TaVNS will be performed on HX1(Erzhong) and CO15(Xin). Ear stimulation acupoints are selected according to auricular acupuncture point with the distribution of vagus nerve [18, 24]. Acupoints of PC6 (Neiguan) and HT7 (Shenmen) will also be stimulated to calm the mind. Ear clip electrodes will be attached to bilateral Erzhong and Xin, skin electrodes will be attached to bilateral PC6 and HT7 with a 10 Hz continuous wave, setting the pulse width of 0.2ms ± 30%.

Usual Care: participants will be encouraged to maintain their routine life if they did not take any medicine; otherwise, they will be allowed to continue their usual medicine treatment for PVCs recommended by the guideline. The usual care used by the patients was not allowed to alter from the whole study period.

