#### Sham-taVNS group

Participants in Sham-taVNS group will receive Sham-taVNS and usual care. The points, stimulator and stimulating parameters used in Sham-taVNS group are the same with taVNS group. However, we cut the inner electric wire of the stimulator to prevent the current output. Usual Care: the same with the taVNS group.

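### Active participants receive current at the ear points and also at PC6 and HT7, sham participants at neither, so the trial tests that combination and cannot credit an effect to taVNS alone

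*Protocol article*

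**What the plan says.** In the protocol article, the taVNS group section ties the name to the ear: "TaVNS will be performed on HX1(Erzhong) and CO15(Xin". It then adds a second site: "Acupoints of PC6 (Neiguan) and HT7 (Shenmen) will also be stimulated to calm the mind". The hardware is separate from the ear clips, and the current is real: "skin electrodes will be attached to bilateral PC6 and HT7 with a 10 Hz continuous wave".

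The Sham-taVNS group section keeps everything but the current. "The points, stimulator and stimulating parameters used in Sham-taVNS group are the same with taVNS group", and "we cut the inner electric wire of the stimulator to prevent the current output". The Blinding section confirms that sham delivers no current.

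The Background gives PC6 and HT7 a cardiac rationale. It says that laboratory work has shown that "needling in PC6 (Neiguan) and HT7 (Shenmen) stabilizes heart rate by blocking ion channels in tachyarrhythmia cardiomyocytes and stimulating parasympathetic nerves".

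The claims name taVNS only. The aim at the end of the Background is the efficacy of taVNS in lowering PVC counts. The Conclusion says "The TASC-V trial will reveal the efficacy and safety of taVNS for frequent PVCs", and the Discussion paragraph of the abstract says much the same. The limitations at the end of the main Discussion cover sample size and follow-up, the unblinded operator, and the absence of a waiting-list group. They do not mention the added stimulation.

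**The concern.** The arms differ in two electrical components, and the claims name one. If the active arm does better, the cause could be the ear stimulation, the PC6/HT7 stimulation, or both. A reader who takes the Conclusion at face value and applies ear stimulation alone would be relying on a treatment that this trial did not test.

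The article's own rationale means the second component cannot be set aside. The Background places it on a rhythm pathway, which bears on the primary outcome. The taVNS group section instead gives it a calming purpose. That reading does not remove the problem, because anxiety (SAS), depression (SDS), insomnia and palpitation are secondary outcomes, and the Discussion links anxiety and depression to arrhythmia.

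**Working it through.** The point concerns attribution, so the main check is a comparison of the sections. The arithmetic only shows what the planned size applies to.

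**1. What each arm receives**

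| Component | Active arm | Sham arm |
|---|---|---|
| Current at HX1 and CO15 (ear clips) | yes | no |
| Current at PC6 and HT7 (skin electrodes) | yes | no |
| Electrodes in place, same device, usual care | yes | yes |

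Sources: taVNS group, Sham-taVNS group and Blinding sections. Write E for ear current and B for current at PC6/HT7. Only the cells (E=1, B=1) and (E=0, B=0) are observed. E and B are identical for every participant, so their separate effects cannot be estimated by any model fitted to these data. A later analysis plan cannot change this.

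**2. What the claims name**

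The aim and the conclusions claim an effect of E. The Sample size section states the null as no difference between the two groups, which is a statement about E and B together. That hypothesis fits the design, whereas the aim and conclusions go beyond it.

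**3. What the planned size powers**

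Inputs from the Sample size section: 58.3% versus 21.1%, two-sided 5%, 90% power, 15% loss, 45 per arm.

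- Difference: 58.3 − 21.1 = 37.2 points; mean rate 39.7%.
- Pooled normal formula: n = [1.96·√(2·0.397·0.603) + 1.282·√(0.583·0.417 + 0.211·0.789)]² / 0.372² = 34.2, so 35 per arm. 35/0.85 = 41.2, so 42 per arm (84 in total).
- With continuity correction: 40 per arm; 40 × 1.15 = 46 (92 in total).
- Fisher's exact test: power 89.65% at 39 per arm; 39/0.85 gives 46 (92 in total).
- The stated 45 per arm (90 in total) is close to the last two. After 15% loss, 45 × 0.85 leaves about 38 per arm, with power 92.8% (pooled normal) or 88.8% (Fisher).

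The planned size is therefore reproduced approximately. It applies to the package against no current.

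**4. Illustration of the ear component alone**

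The article gives no component-specific rate and does not say whether the pilot used PC6 and HT7. Assume that it did, that the effects add, and that 38 per arm are evaluable. If the ear component carries a share f of the 37.2 points, an ear-only arm would respond at 21.1% + f × 37.2%. Power is Φ{[d − 1.96·√(2·p̄·q̄/38)] / √[(p₁q₁ + p₂q₂)/38]}, where d is the ear-only difference:

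| Share f | Ear-only rate | Power against sham |
|---|---|---|
| 100% | 58.3% | 93% |
| 75% | 49.0% | 73% |
| 50% | 39.7% | 42% |
| 25% | 30.4% | 15% |

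These shares are assumed, not estimated. The table shows only that support for the package does not carry over to ear stimulation by itself.

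**The case against.** The strongest defence is that the regimen is openly described and the comparison is sound. Sham is matched on points, device and settings, and anyone reading the Methods can see what is delivered. Type I error, the sample size and the primary outcome are unaffected. The article also calls itself a preliminary evaluation, and separating components is a reasonable task for a later trial. All of that stands. It supports naming the package as a package and does not justify a conclusion about one part of it. Calling the study preliminary does not tell the reader that a second stimulated site was involved.

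Four stronger readings are tempting and are not supported:

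- *The comparison is invalid.* It is not; package against inactive package is a proper randomised contrast.
- *PC6/HT7 stimulation is shown to be active here.* The Background cites laboratory needling studies and heart rate. The trial uses skin electrodes and counts PVCs in patients. A contribution is plausible, not demonstrated.
- *The formal hypothesis is wrong.* It compares the two groups and names no component.
- *No safety finding can be assigned to the ear.* Ear clips and skin electrodes sit at different sites, so a local reaction can be assigned by location. Only systemic events cannot be.

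**Conclusion.** The point holds in this form: the trial can show whether ear plus PC6/HT7 stimulation differs from no current, and it cannot show how much of any difference, or of any systemic adverse event, belongs to auricular vagus stimulation. The aim and the conclusions claim more than that.

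Its size cannot be put as an estimate. If neither component works against the other and they do not interact, the ear share of the effect lies anywhere from 0 to 100%; without those assumptions even that range is not guaranteed. The finding itself rests only on the intervention sections and needs no assumption about whether PC6/HT7 stimulation works.

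A smaller inconsistency goes with it: the Background gives these points a rhythm rationale, while the taVNS group section gives them a calming one.

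**What to change.** - In the aim, the intervention label and the conclusions (abstract and main text), name the tested intervention as taVNS combined with transcutaneous electrical stimulation at PC6 and HT7.
- Limit the efficacy and safety conclusions to that combination.
- Add to the limitations that the two components were always given together, so their effects cannot be separated.
- Reconcile the purpose of PC6/HT7 stimulation between the Background and the taVNS group section.

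The cost is a few sentences and a narrower claim. The null hypothesis, the sample size, the data collected and the treatment participants receive all stay as they are.
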